#### Participant withdrawal

In the event of patients wishing to discontinue in the trial, the participant would be withdrawn from the study with the assurance that their usual care will continue unaffected. Identifiable data or tissue already collected with consent would be retained and used in the study. No further data or tissue would be collected, or any other research procedures carried out on or in relation to the participant. If the patient consented to have long-term electronic tracking of their outcomes, this would be continued.

#### Statistics

The principle parameters being examined in work package 1 are hospitalisation, mortality, and their association with frailty. Based upon US data [6], we have assumed an adjusted risk ratio of 2.24 for 1-year mortality and 1.56 for 1-year mortality and/or hospitalisation for frail versus non-frail patients receiving haemodialysis. We have assumed a baseline (non-frail) risk of 5% for 1-year mortality and a 40% risk of 1-year mortality/hospitalisation, powered to 0.8 and with a confidence interval of 0.95. We therefore calculate a sample size of 602 to be adequately powered to demonstrate a difference in 1-year mortality or 150 patients to be powered for 1-year mortality/hospitalisation.

Work package 2 is designed as a feasibility study so no specific power calculations have been made. However, one of the secondary outcomes is to use the data regarding effect sizes to determine the sample required for a larger multi-centre study based upon the feasibility of work package 2.

Statistical analysis will be performed using standard software (SPSS Version 25, Mac version, Chicago, USA). Normality of data will be assessed using the Kolmogorov-Smirnov tests. Paired sample *t* test and Wilcoxon signed rank test, for parametric and non-parametric data respectively, will be used to compare the means of two variables from a single group. Comparison of data between groups will be made using unpaired student *t* tests and the Mann-Whitney test for parametric and non-parametric data, respectively. Categorical data will be analysed using Pearson’s or Spearman’s test as appropriate. A *p* value < 0.05 is considered significant in the statistical analysis.

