#### Recruitment and consent

Potential participants will be identified through their previous participation in work package 1. Patients scored as “pre-frail” will randomly be selected to participate in work package 2. Patient information sheets will be given to the patients in advance of a discussion with the researcher either by post or in person. Individuals will be approached at their usual dialysis unit appointment for discussion and potential recruitment to the study. Potential participants will be given the opportunity to reflect on the information given both verbally and within the written information sheet. No fixed time is specified for the length or timing of this prior interview as it will be dependent upon the patient’s understanding of their underlying disease and of the research project. A certain level of English proficiency will be necessary to participate in the intervention, however it is important that non-native English speaking patients are given full opportunity to participate in this study and the same methods will be used as in work package 1 to facilitate this. Written consent will be received from each patient entering the study. A study patient identifier will be allocated and recorded on the study recruitment log.

Work package 1 patients who meet eligibility criteria will be randomly selected for participation in work package 2 using REDCap™ (in random permuted blocks within strata to balance numbers and characteristics). Participants who have subsequently been approached and given consent to participate in work package 2 will be randomised once more using REDCap™ (in random permuted blocks within strata to balance numbers and characteristics) into one of the following lifestyle intervention groups (*n* = 25 for each intervention group for a total of 50 participants). As part of the cm-RCT design, data from pre-frail work package 1 patients who were eligible but not selected for participation in work package 2 will provide a further comparator group for analysis. As an open-label study, neither participants nor researchers will be blinded to group allocation.

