#### Passive control group

This group will receive their usual standard of care from their treating dialysis centre, including usual dietitian input. However, there will be no psychosocial intervention or focused exercise and dietary monitoring programme. Follow-up will be at routine clinic visits only, where lifestyle modification advice will be reinforced as per usual clinical practise. Physiotherapy may be offered to these patients as per standard referral guidelines but will not have the psychosocial underpinning of the intervention group.

Both groups will undergo a repeat frailty testing during the mid-point (3 months ± 2 weeks) and the end of study intervention (6 months ± 2 weeks) (see Figs. 1 and 2). The aim is to assess if there is any change in frailty status which will provide data to underpin a power calculation for a subsequent large-scale study. Additional pre-specified secondary outcomes will be collected as highlighted below in the protocol. Participants will also be invited to complete a series of questionnaires to ascertain the tolerability and suitability of the intervention trial, and to guide the delivery of the trial on a larger scale.

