Work package 2 is an unblinded, randomised controlled study using a psychologically supported multi-disciplinary intervention into frailty compared with a control group which receives standard care. This will be used as a basis for exploring whether a large scale, multi-centre trial is feasible and warranted, while also providing data upon effect sizes to allow subsequent power calculation for such a study. We chose the “pre-frail” group as the focus of this intervention, firstly because they arguably have the most to gain—not progressing to frailty—and, secondly, because pre-frailty represents a much less heterogeneous group than frailty, the latter of which would include essentially functionally independent individuals with a few accumulated deficits along with bed-bound individuals and those approaching end-of-life. The pre-frail group therefore have an easily definable set of characteristics and have the ability to participate in, and benefit from, the proposed interventions.

One of the principle strengths of the study design is the breadth of data being collected. Researchers will collect data on multiple aspects of frailty from consenting patients to include aspects of sarcopenia (muscle mass, quality, and function), immunosenescence, functional status/disability, mood, cognitive status, and medical history. This rich dataset will allow detailed analysis of the heterogeneity or otherwise of frailty within the cohort. As work package 1 is a single time-point analysis with electronic follow-up thereafter, dropout should be minimal and large numbers of patients could be recruited to allow such detailed analysis to have real meaning to clinicians. Another strength lies in the cm-RCT design, whereby stratified random sampling will identify trial participants from consenting eligible cohort study participants. This approach has several benefits, including amelioration of potential attrition bias in the control group, long-term data follow-up for a large comparator group, and increased power for the study [34].

A weakness of the study is the single time-point assessment in work package 1, as frailty is known to change over time [45–47]. Nevertheless, objective frailty measurements still hold prognostic value [48].

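### The definitive trial is to be sized from effect sizes observed in 25 patients per arm, which are too imprecise to set its target difference

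*Protocol article*

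**What the plan says.** Work package 2 randomises "25 for each intervention group for a total of 50 participants" (Protocol article, Recruitment and consent). The Statistics section explains that "Work package 2 is designed as a feasibility study so no specific power calculations have been made". Its next sentence gives the study a quantitative purpose all the same: "one of the secondary outcomes is to use the data regarding effect sizes to determine the sample required for a larger multi-centre study".

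Two other places carry the same plan. Under Passive control group, the repeat frailty tests at 3 and 6 months are meant to show any change in frailty status, "which will provide data to underpin a power calculation for a subsequent large-scale study". In the Discussion, work package 2 is to explore whether a large trial is feasible and warranted, "while also providing data upon effect sizes to allow subsequent power calculation for such a study".

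None of these places names a minimum important difference, allows for the uncertainty of the observed effect, or limits the input to the SD or the event rate.

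**The concern.** A sample size depends on the inverse square of the target difference, so an error in that difference is magnified. If the target is the effect seen in a small pilot, chance largely decides the size of the next trial. A pilot that happens to look good yields a trial that is too small. One that happens to look weak yields a trial too large to run, and one at or below zero yields no usable size.

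The article leaves many details to the full protocol, but this is not one of them. It states the use of the effect sizes as an output of work package 2. At stake is the power of a later multi-centre trial. The primary feasibility endpoint (recruitment, loss to follow-up, withdrawal) is not affected.

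**Working it through.** **The plan's own figures.** Work package 2 has no power figure to reproduce. The two work package 1 sizes do reproduce, with two proportions, equal groups, two-sided alpha 0.05, power 0.80 and unpooled variance: n per group = (1.96 + 0.842)² × [p1(1 − p1) + p2(1 − p2)] / (p1 − p2)².
- Mortality: 5% against 5% × 2.24 = 11.2% gives 301 per group, 602 in total, as stated.
- Mortality/hospitalisation: 40% against 40% × 1.56 = 62.4% gives 75 per group, 150 in total, as stated.

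**Inputs for work package 2.** 25 per arm (Recruitment and consent); significance level 0.05, taken as two-sided (Statistics); a 14.7% reduction in frailty at 12 months in older people generally (Background), the only intervention effect on frailty cited. The article gives no SD and no control rate for the frailty outcomes, so these are assumed over a range.

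**Precision, continuous outcome.** SE of a standardised difference = √(2/n).
- n = 25: √(2/25) = 0.283; × 1.96 = 0.55 SD.
- n = 20 analysed: √(2/20) = 0.316; × 1.96 = 0.62 SD.

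**Precision, binary outcome.** Reading 14.7% as an absolute difference, p2 = p1 − 0.147 and SE = √[p1(1 − p1)/25 + p2(1 − p2)/25].

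| Assumed control rate | SE (points) | 95% half-width (points) |
|---|---|---|
| 20% | 9.2 | 18.0 |
| 30% | 11.7 | 22.8 |
| 40% | 13.1 | 25.7 |
| 50% | 13.8 | 27.1 |
| 70% | 13.5 | 26.5 |

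Every half-width exceeds 14.7 points.

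**Consequence for the next trial.** The size needed per arm at a true effect d is 2 × (1.96 + 0.842)² / d². For each d, 1,000,000 pilots of 25 per arm were simulated, the observed effect was put into this formula, and the result was compared with the size needed at the true effect. A trial is undersized if its computed size is below the size needed, which means true power under 80%.

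| True effect (SD) | Needed per arm | Pilots with a positive effect | Undersized, of all pilots | Undersized, of positive pilots | Mean true power, positive pilots | Computed size per arm, positive pilots: median (5th to 95th percentile) |
|---|---|---|---|---|---|---|
| 0.2 | 393 | 76% | 50% | 66% | 56% | 190 (31 to 14,156) |
| 0.3 | 175 | 86% | 50% | 59% | 65% | 126 (24 to 6,562) |
| 0.4 | 99 | 92% | 50% | 55% | 70% | 85 (20 to 2,820) |
| 0.5 | 63 | 96% | 50% | 52% | 73% | 59 (16 to 1,191) |
| 0.8 | 25 | 99.8% | 49% | 50% | 77% | 25 (9 to 137) |

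The two undersized columns agree with a hand calculation. The observed effect exceeds the true one about half the time, so the share among positive pilots is about 0.50 divided by the share that are positive. At 0.2 SD this is 0.50/0.76 = 0.66.

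The binary version, with a true difference of 14.7 points and control rates of 30% to 70%, gives 52% to 53% undersized over all pilots and 60% to 64% among positive ones.

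**What 50 patients can estimate.** With 48 degrees of freedom, the 95% interval for the SD runs from 0.83 to 1.25 times its estimate. Sample size varies with the SD squared, so for a fixed target difference this changes it by factors of about 0.83² = 0.69 to 1.25² = 1.56. That is usable; 24 to 6,562 per arm when 175 are needed is not.

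**The case against.** The wording can be read more loosely. Data that underpin or allow a power calculation could mean SDs and event rates, and the Statistics sentence goes on to tie the larger study to the feasibility of work package 2. The later trial will also need its own protocol and its own justification of size. This stands for the Passive control group and Discussion passages. It does not remove the Statistics sentence, where effect sizes are the named input that determines the sample.

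A reader might infer more than the article supports:
- **That the error exceeds any plausible effect.** The standard error, 0.28 SD, is below a moderate effect of 0.4 SD, and the half-width, 0.55 SD, is below a large one of 0.8 SD. The article gives no plausible range for its frailty outcomes.
- **That the next trial would be under-powered more often than not.** Over all pilots it is about half. The share rises above half only if the next trial follows a positive result, and the article states no such rule.
- **That a near-zero difference would lead to a wrong decision not to proceed, or that a test at p < 0.05 drives the sizing.** No passage ties either to the sample-size step. The significance level is a general statement covering both work packages.

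The comparator group of pre-frail patients not selected for work package 2 does not rescue the estimate. The Discussion describes work package 1 as a single time-point assessment, so these patients have no repeat frailty measurement.

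**Conclusion.** The concern holds in a limited form. The effect observed with 25 per arm is too imprecise to set the target difference of the definitive trial. Its 95% half-width is larger than effects up to about 0.5 SD, and larger than the one intervention effect that the article cites. Sizing on it makes adequate power roughly a coin toss, and worse than that after a positive pilot unless the true effect is large.

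The figures assume a normal outcome, two-sided 5% alpha, 80% nominal power and no dropout unless stated. The actual endpoints are the Fried Frailty Phenotype and the Clinical Frailty Scale, which are not obviously normal; the binary version points the same way. The comparison with 14.7% assumes that this is an absolute difference and that a 12-month effect in older people generally is a fair yardstick for a 6-month intervention in haemodialysis patients.

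The correction is worth making because it concerns a declared output of work package 2. It leaves the primary endpoint as it is.

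**What to change.** Replace the sentence in the Statistics section, and align the statements under Passive control group and in the Discussion, with wording such as:

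*The definitive trial will be powered for a minimum important difference justified independently of the effect observed in work package 2, which will supply the outcome SD or control-arm event rate (with allowance for its uncertainty), baseline to follow-up correlation, recruitment and retention.*

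The allowance can take several forms. An upper one-sided 80% limit for the SD, 1.10 times its estimate with 48 degrees of freedom, is one convention and is optional.

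Report work package 2 between-arm differences as estimates with 95% confidence intervals, without significance claims.

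The cost is wording, plus the work of justifying a minimum important difference. The drawback is that the next trial may need more patients than an optimistic pilot estimate would suggest.

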#### Secondary endpoints

Secondary endpoints include: 1) refinement of the multi-disciplinary intervention based upon views from participants and stakeholders (from post-study questionnaires); 2) change in frailty status (based on Fried Frailty Phenotype, Clinical Frailty Scale); 3) difference in clinical and biochemical outcomes; 4) quality of life score (EQ-5D-3 L); 5) receipt of kidney transplant; 6) vascular access failure; and 7) long-term clinical outcomes (death, cardiac events, hospitalisation) to University Hospital Birmingham electronic patient records and Hospital Episode Statistics

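### Work package 2: the stated between-group tests adjust for neither baseline nor randomisation strata, a normality pre-test chooses the test, and paired within-arm tests do not estimate the intervention effect

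*Protocol article*

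**What the plan says.** The Statistics section lists the tests once, for both work packages:

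- Choice of test: "Normality of data will be assessed using the Kolmogorov-Smirnov tests".
- Between groups: "Comparison of data between groups will be made using unpaired student" t tests, or Mann-Whitney if the data are judged non-parametric.
- Within a group: paired t or Wilcoxon signed rank tests "will be used to compare the means of two variables from a single group".
- Categorical data go to Pearson's or Spearman's test.
- Threshold: a p "value < 0.05 is considered significant in the statistical analysis".

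No covariate-adjusted, stratified or repeated-measures analysis is named.

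The design of work package 2 provides more than these tests use. Under Recruitment and consent, participants are randomised "in random permuted blocks within strata to balance numbers and characteristics", with 25 "for each intervention group for a total of 50 participants". A baseline assessment precedes this in work package 1. Under Passive control group, "Both groups will undergo a repeat frailty testing during the mid-point" (3 months) and again at 6 months. Secondary endpoint 2 is "change in frailty status (based on Fried Frailty Phenotype, Clinical Frailty Scale"). The Statistics section and the Discussion both say that effect sizes from work package 2 will be used to size a larger multi-centre trial.

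**The concern.** Three features of the stated method fit a 50-patient randomised comparison with repeated measures poorly.

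1. An unpaired test of follow-up values leaves the baseline out. An unpaired test of change scores subtracts it but does not adjust for it. The article does not say which is meant. Neither version uses the strata.
2. The test is chosen by a normality result that is unreliable at 25 per arm.
3. Paired tests within one arm answer a different question from the randomised comparison. The Discussion notes that frailty changes over time, so some within-arm change is expected without any intervention.

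The stake is the quality of the effect estimate that the next trial will be built on. There is also some risk that a significant change in the active arm alone is taken for benefit.

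**Working it through.** **The plan's own figures.** The only computed sample sizes are for work package 1. With two proportions, unpooled variance, two-sided alpha 0.05 and power 0.80, n per group = (1.960 + 0.842)² × [p1(1−p1) + p2(1−p2)] / (p1−p2)².

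- 5% against 5% × 2.24 = 11.2%: 301 per group, 602 in total.
- 40% against 40% × 1.56 = 62.4%: 75 per group, 150 in total.

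Both match the article and are untouched by this point. Work package 2 has no power figure to reproduce.

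**Where the paired tests apply.** The Discussion describes work package 1 as assessed at a single time point with electronic follow-up. Paired comparison of frailty from baseline to follow-up can therefore only arise in work package 2.

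**Precision of the between-arm comparison.** Inputs: 25 per arm (Recruitment and consent), and the baseline to follow-up correlation r, which the documents do not give; 0.5 to 0.8 is assumed. With equal SDs at both times, the variance in units of the follow-up variance is 1 for follow-up values, 2(1−r) for change scores and 1−r² for baseline adjustment. The ratio of adjustment to change scores is (1−r²)/[2(1−r)] = (1+r)/2.

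| r | follow-up | change | adjusted | saving v. follow-up | saving v. change |
|---|---|---|---|---|---|
| 0.5 | 1 | 1.00 | 0.75 | 25% | 25% |
| 0.7 | 1 | 0.60 | 0.51 | 49% | 15% |
| 0.8 | 1 | 0.40 | 0.36 | 64% | 10% |

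At a lower correlation of 0.3 the variances are 1, 1.40 and 0.91, so the savings are 9% and 1 − 0.91/1.40 = 35%.

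The difference detectable with 80% power is (1.960 + 0.842) × √(2 × variance / 25), in SD units, for follow-up, change and adjusted analyses in turn:

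- r = 0.5: 0.79, 0.79, 0.69.
- r = 0.7: 0.79, 0.61, 0.57.
- r = 0.8: 0.79, 0.50, 0.48.

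Simulated power for a 0.5 SD effect (20,000 runs) is 41%, 41% and 51% at r = 0.5, and 42%, 61% and 67% at r = 0.7. With no effect, all three reject about 5% of the time.

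**Within-arm paired tests.** Suppose both arms truly change by the same amount m, so the intervention has no effect. The SD of change is √[2(1−r)]. Let P be the power of a paired t test with 25 patients, from the noncentral t with 24 degrees of freedom and noncentrality 5m/√[2(1−r)]. The arms are independent, so the chance that only the active arm is significant is P(1−P).

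| r | m (SD) | P | active arm only |
|---|---|---|---|
| 0.5 | 0.3 | 0.30 | 21% |
| 0.5 | 0.4 | 0.48 | 25% |
| 0.7 | 0.3 | 0.46 | 25% |
| 0.7 | 0.4 | 0.70 | 21% |

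Simulation agrees (21% to 25%). Exactly one arm, either one, is significant in twice that proportion, about 42% to 50%.

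**The normality gate at n = 25.** With the Lilliefors correction, simulated Kolmogorov-Smirnov rejection rates are 22% and 40% for moderately skewed data (gamma, shape 4 and 2), 68% for exponential data, and 90% for a roughly normal score rounded to 7 points. Without the correction, the rate for exponential data is about 8%. The article does not say which form applies. The check thus often passes skewed data, and it rejects a rounded ordinal score mainly because it is discrete.

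**The case against.** The strongest reply is that nothing invalid is planned. Randomisation protects the unpaired tests, their type I error stays near 5%, and ignoring strata tends to err on the conservative side. The strata are not named, so their prognostic value is unknown. The list is generic, the primary endpoint is feasibility, no power is claimed for work package 2, and a fuller plan may hold outcome-specific models. All of this stands and limits the importance. It does not remove the point, because the article states its tests and those tests make no use of information that the design already provides.

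Several stronger readings are tempting and not supported:

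- *Baseline is ignored altogether.* The endpoint is change in frailty status; an unpaired test on change scores would use baseline, though inefficiently. The larger savings of 25–64% apply only if follow-up values are compared.
- *EQ-5D and physical measures are also repeated at 3 and 6 months.* The text gives those times only for frailty testing, and the schedule figure is not shown.
- *Within-arm change is inflated by regression to the mean.* Participants are chosen from a middle band, so the size and direction of any regression are unclear. Natural change over time carries the argument.
- *A Mann-Whitney test leaves no effect size.* A location shift or a rank-based effect can be reported with it.
- *The investigators will claim efficacy from within-arm p values.* Nothing says so, and the Discussion describes a comparison with a control group.

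A linear model also does not suit every named endpoint: the Clinical Frailty Scale and frailty category are ordinal.

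**Conclusion.** The point holds as one of precision and interpretation, not of validity. The unpaired comparisons are sound under randomisation but give up 10–25% of variance against change scores, or 25–64% against follow-up values, at an assumed correlation of 0.5–0.8. These figures are for continuous measures; the gain for ordinal outcomes was not calculated, and neither was any further gain from the strata. The paired tests do not estimate the intervention effect. With equal true change of 0.3–0.4 SD in both arms (assumed) and a correlation of 0.5–0.7, they single out the active arm in about 21–25% of trials. The normality check is a poor basis for choosing a test at this size. Importance is minor to moderate: these are secondary endpoints of a feasibility trial, but their effect sizes are meant to inform a larger one.

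**What to change.** For work package 2 outcomes measured at baseline and follow-up, replace the generic list with the following:

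- Report the between-arm difference with a 95% CI from a model with arm, baseline value and the randomisation strata, keeping strata terms few.
- For continuous measures, use a linear model, or a mixed model where both 3- and 6-month values exist, with a bootstrap CI if residuals are skewed.
- For the Clinical Frailty Scale and Fried category, use an ordinal model.
- Do not let a Kolmogorov-Smirnov result choose the test.
- Report within-arm change descriptively, without p values.

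For the frailty outcomes this needs no new data or visits. The cost is slightly more analysis work and a few degrees of freedom out of 50 participants.

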## Aims

This study aims to: 1) measure prevalence and outcomes associated with frailty in a large UK haemodialysis cohort; 2) determine the optimum frailty assessment tool for UK patients receiving haemodialysis, as defined by predictive value for mortality/hospitalisation; and 3) conduct a feasibility study exploring a multi-disciplinary clinical intervention to improve frailty status among patients receiving haemodialysis

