#### Baseline assessment

Prior to the patient being connected to the dialysis machine, the following assessments will take place: 1) timed walk over 4 m; 2) assessment of grip strength with a dynamometer; and 3) Montreal Cognitive Assessment (MoCA)

When the patient is dialysing, the following assessments will be performed: 1) quadriceps ultrasound assessment; 2) questionnaires will be given to participants in either paper or electronic format via a tablet device, according to patient preference, including the 3-level version of the EuroQol five dimensions (EQ-5D-3 L) and the Patient Health Questionnaire (PHQ)-9 (where a PHQ-9 score of 20 or over may indicate depression and a discussion will be held with the patient asking whether they would like a discussion with their nephrologist or a referral to the renal psychology service); and 3) a questionnaire related to each frailty instrument, demographic data, and social history (level of education, employment status, nature of employment, smoking, and alcohol history).

EPRs will be interrogated for data on comorbidities, dialysis parameters, previous transplantation, biochemical data, medication history, and social deprivation score.

The patient’s nephrologist will be invited to complete a Clinical Frail Scale for individual participants within 1 month of the baseline clinical assessment.

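### Work package 1 is sized on an adjusted risk ratio and ranks frailty tools by predictive value, but the named analyses are all unadjusted and none formally compares tools

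*Protocol article*

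**What the plan says.** All references are to the protocol article.

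- **Main question (Statistics).** "The principle parameters being examined in work package 1 are hospitalisation, mortality, and their association with frailty".
- **Target effect (Statistics).** For death alone the planning value is given thus: "we have assumed an adjusted risk ratio of 2.24 for 1-year mortality". The composite has its own planning ratio, stated as "1.56 for 1-year mortality and/or hospitalisation for frail versus non-frail patients receiving haemodialysis". The non-frail risk of death is set as follows: "We have assumed a baseline (non-frail) risk of 5% for 1-year mortality". The corresponding figure for the composite is "a 40% risk of 1-year mortality/hospitalisation". The resulting totals are 602 for mortality and 150 for the composite.
- **Aim 2 (Aims).** The study is to "determine the optimum frailty assessment tool for UK patients receiving haemodialysis, as defined by predictive value for mortality/hospitalisation". The Discussion says the instruments will be compared through their association with adverse outcomes.
- **Named analyses (Statistics).** Kolmogorov-Smirnov for normality; paired t or Wilcoxon signed rank within a group; unpaired t or Mann-Whitney between groups; and for categorical data, "Categorical data will be analysed using Pearson’s or Spearman’s test as appropriate". Significance is p < 0.05.
- **Timing (Baseline assessment).** The nephrologist is invited to "complete a Clinical Frail Scale for individual participants within 1 month of the baseline clinical assessment". Under Data handling, outcome time points run from recruitment, out to 5 years.

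**The concern.** The planning effect is adjusted and the outcomes are binary or time-to-event, yet no named method takes a covariate, an event time or a censoring time. Frailty travels with age and comorbidity, so an analysis confined to the list would give a confounded association. The article argues that North American results do not carry over to the UK. A crude UK ratio set beside the adjusted US ratio used for planning would not test that like for like.

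Aim 2 is a different problem. All tools are measured on the same patients, so choosing between them needs a prediction measure for each tool and a paired comparison of those measures. The listed paired tests compare means of two variables, which says nothing about which variable predicts better. Spearman's coefficient, one reading of the categorical-data sentence, is a rank correlation and poorly suited to a yes/no outcome by frailty group.

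A lesser matter is that the Clinical Frailty Scale may be scored after follow-up has begun, so an early admission could inform that score but not the others.

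**Working it through.** **1. Reproduce the sample size.** Inputs from Statistics: risks 5% and 5% × 2.24 = 11.2%; 40% and 40% × 1.56 = 62.4%; power 0.80; 95% confidence. Assumed because not stated: two-sided alpha 0.05 and equal numbers of frail and non-frail patients.

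n per group = (1.96 + 0.842)² × [p0(1 − p0) + p1(1 − p1)] / (p1 − p0)²

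- Mortality: 7.85 × (0.0475 + 0.0995) / 0.062² gives 301 after rounding up, so 602 in total.
- Composite: 7.85 × (0.2400 + 0.2346) / 0.224² gives 75 after rounding up, so 150 in total.

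Both stated totals reproduce exactly. The formula is a crude comparison of two proportions with an adjusted ratio as its input; it contains no adjustment.

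**2. Set each need against the list.**

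- *Crude 1-year difference, frail versus non-frail:* covered if Pearson's means chi-square. The 2×2 table also gives a crude risk ratio and crude predictive values.
- *Adjusted risk ratio:* not covered.
- *Event time and censoring over 5 years:* not covered.
- *Discrimination of one tool:* obtainable by dividing the Mann-Whitney statistic by the product of the group sizes, though the article does not state this use.
- *Formal comparison of tools in the same patients:* not covered.

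**3. How far crude and adjusted could differ (illustration).** Let one binary confounder have prevalence c1 in frail and c0 in non-frail patients and risk ratio R for death. All three are assumed.

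Crude RR = 2.24 × [1 + c1(R − 1)] / [1 + c0(R − 1)]

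- c1 = 0.5, c0 = 0.3, R = 2: factor 1.5/1.3 = 1.15, crude RR 2.58.
- c1 = 0.6, c0 = 0.3, R = 2.5: factor 1.90/1.45 = 1.31, crude RR 2.94.
- c1 = 0.7, c0 = 0.3, R = 3: factor 2.4/1.6 = 1.50, crude RR 3.36.

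**4. What adjustment costs in power.** If covariates explain a share R² of frailty (assumed), the total needed is 602/(1 − R²). Power at 602 is obtained by replacing 301 per group with 301(1 − R²), using the pooled-variance normal approximation, which gives 79.8% with no adjustment.

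| Assumed R² | Total needed | Power at 602 |
|---|---|---|
| 0.05 | 634 | 78% |
| 0.10 | 669 | 75% |
| 0.20 | 753 | 70% |
| 0.30 | 860 | 65% |

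Expected deaths in year 1, with half frail: 301 × 0.05 + 301 × 0.112 ≈ 49, so the covariate list has to be short.

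**5. Events before a late Clinical Frailty Scale.** Assume half frail and a constant hazard over the year.

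- Non-frail monthly risk: 1 − 0.6^(1/12) = 4.2%.
- Frail monthly risk: 1 − 0.376^(1/12) = 7.8%.
- First composite events in month 1: 301 × 4.2% + 301 × 7.8% ≈ 36 of 602.

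All 36 precede the score only if every scale is completed at month end. If scoring is spread evenly over the month, about half do, or 18.

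**The case against.** The strongest defence is that the test list is generic. It follows the work package 2 paragraph and serves both work packages; the paired tests suit work package 2's repeat assessments, since work package 1 assesses patients once. Nothing says the list is exhaustive, the adjusted 2.24 is a planning input rather than a declared estimand, and a condensed article commonly leaves models to an analysis plan. It stands that the mere absence of a model would be no finding. But this article does name its methods, and those methods do not fit its own planning effect or its own definition of the optimum tool.

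Several stronger readings are tempting, and the document does not support them:

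- *That the listed tests yield nothing usable.* A 2×2 table gives a crude risk ratio and predictive values, and a rescaled Mann-Whitney statistic is one tool's C-statistic.
- *That tools will be ranked by p value.* No section says so.
- *That confounding invalidates Aim 2.* Choosing the best predictor needs no confounder adjustment; the 2.6 to 3.4 range has no bearing on it.
- *That 602 is miscalculated.* It reproduces exactly on its stated inputs.
- *That the Clinical Frailty Scale gains a demonstrated advantage.* The wording allows later scoring without requiring it, one month is the outer limit, and recent inpatients (other than for vascular access) are excluded, which may lower early risk. No effect on discrimination has been shown.

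**Conclusion.** The point holds as a mismatch between stated methods and stated targets. Following the list would give a crude association for the principal question and no formal comparison of tools for Aim 2. Data collection is unaffected, and the wording can be corrected before outcomes are analysed.

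The possible gap between crude and adjusted ratios (2.6 to 3.4 against 2.24) rests wholly on assumed confounder values; it shows that the choice can matter, not how much it will in this cohort. The loss of power under adjustment likewise depends on an assumed R². The Clinical Frailty Scale timing is secondary: 36 patients is the figure for the latest permitted scoring with half frail and constant hazard, and about 18 is the figure for evenly spread scoring. The main point stands without it.

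**What to change.** For work package 1, replace the generic test list with:

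1. **Association question.** 1-year risk ratios with 95% CIs from modified Poisson or log-binomial regression, and Cox models for longer follow-up. Report them crude and adjusted for a short pre-specified set of baseline covariates drawn from the data already planned, such as age, sex, comorbidity, dialysis parameters and deprivation.
2. **Aim 2.** C-statistic of each tool for 1-year mortality/hospitalisation in patients with all tools scored, with paired (DeLong or bootstrap) 95% CIs for the differences and no confounder adjustment.
3. **Sensitivity analysis only.** Repeat item 2 counting events for every tool from the date of the Clinical Frailty Scale.
4. **Wording.** State that Pearson's means the chi-square test for frailty group by binary outcome, and drop Spearman for that purpose.

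No new measurements are needed beyond recording the date of the Clinical Frailty Scale. The costs are some additional analysis; the lower power for the adjusted mortality comparison shown in the working, which should be acknowledged beside the 602; and the loss from the paired comparison of patients without a nephrologist score, because nephrologists are only invited to give one. The number lost should be reported. The sensitivity analysis also drops patients who die before they are scored and the events that precede the score.
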